**Materials and methods::**

The present manuscript describes the procedures of the VIABILITY trial, a descriptive prospective single-center cohort study. The main purpose of this trial is to assess the link between systemic inflammation, pan-coronary plaque vulnerability (referring to the plaque vulnerability within the entire coronary tree), myocardial viability and ventricular remodeling in patients who had suffered a recent ST-segment elevation acute myocardial infarction (STEMI). One hundred patients with STEMI who underwent successful revascularization of the culprit lesion in the first 12 hours after the onset of symptoms will be enrolled in the study. The level of systemic inflammation will be evaluated based on the serum biomarker levels (hs-CRP, matrix metalloproteinases, interleukin-6) in the acute phase of the myocardial infarction (MI) and at 1 month. Pan-coronary plaque vulnerability will be assessed based on serum biomarkers known to be associated with increased plaque vulnerability (V-CAM or I-CAM) and at 1 month after infarction, based on computed tomographic angiography analysis of vulnerability features of all coronary plaques. Myocardial viability and remodeling will be assessed based on 3D speckle tracking echocardiography associated with dobutamine infusion and LGE-CMR associated with post-processing imaging methods. The study population will be categorized in 2 subgroups: subgroup 1 - subjects with STEMI and increased inflammatory response at 7 days after the acute event (hs-CRP ≥ 3 mg/dl), and subgroup 2 - subjects with STEMI and no increased inflammatory response at 7 days (hs-CRP < 3 mg/dl). Study outcomes will consist in the rate of post-infarction heart failure development and the major adverse events (MACE) rate.

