### Study objectives

1.2

The *primary objective* consists in the evaluation of the relationship between coronary inflammation-mediated plaque vulnerability, myocardial viability and ventricular remodeling in the post-infarction period.

The *secondary objectives* of the study are:

(1)to assess the effect of systemic inflammation on the structural remodeling process of the left ventricle (LV) following an AMI and(2)to evaluate the impact of local inflammatory response on pan-coronary plaque vulnerability in the post-infarction period.

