### Study population and subgroups

2.5

This study will enroll 100 patients with STEMI meeting the inclusion criteria. Study subjects will be distributed in 2 groups: group 1 – patients with STEMI and increased inflammatory response at 7 days after the acute event (hs-CRP ≥ 3 mg/dl) and group 2 - subjects with STEMI and no increased inflammatory response at 7 days (hs-CRP <3 mg/dl).

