#### Biomarkers assays

2.6.1

Routine biochemistry and CBC analysis will be performed at the main laboratory of the Emergency Clinical County Hospital of Tirgu-Mures, immediately after randomization. Inflammatory status (hs-CRP levels) will be evaluated at 7 days after the acute cardiac event via immunoturbidimetric assay. Adhesion molecules (VCAM, ICAM), matrix metalloproteinase 9, and interleukin-6 serum levels will be evaluated using enzyme linked immunosorbent assay. Serum inflammatory biomarkers will be analyzed in Advanced Medical and Pharmaceutical Research Center of the University of Medicine and Pharmacy Tirgu-Mures, Romania. N-terminal prohormone of brain natriuretic peptide (NT-proBNP) levels will be evaluated at randomization and at the last follow-up visit, at the main laboratory of the Emergency Clinical County Hospital of Tirgu-Mures by electrogenerated chemiluminescence.

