#### 2D transthoracic echocardiography

2.6.2

Transthoracic echocardiographic (TTE) assessment will be performed at first and last follow-up visit in all patients. Evaluation of cardiac diameters and volumes, systolic and diastolic performance of LV, speckle tracking, and Dobutamine viability test will be conducted with a Vivid E9 ultrasound system (General Electric Vingmed Ultrasound, Horten, Norway), with the patient turned slightly on his left side, according to American College of Echocardiography indications. Left ventricular end-systolic volume (LVESV), left ventricular end-diastolic volume (LVEDV), and left ventricle ejection fraction (LVEF) will be evaluated using the Simpson's method, on the basis of images obtained from apical four chamber view. All measurements will be calculated as an average from 3 heart cycles.

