### Sample size

2.10

One hundred patients with STEMI who underwent successful revascularization of the culprit lesion within the first 12 hours after the onset of symptoms will be enrolled in this study. On the basis of the persistence of systemic inflammation at 7 days after the acute event patients will be allocated into 2 subgroups. Stat Mate 2.0 software was used in order to establish the sample size of the study. According to this computation, a sample size of 50 subjects per group presents a 90% power to detect an increase in major adverse CV events rates proportion of 3.28, with a significance level (alpha) of 0.05 (2-tailed). Therefore, the study population was established at 100 subjects.

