### Statistical analysis

2.11

Graph Pad in Stat 3.10 software (GraphPad Software, San Diego, CA) will be used in order to perform all the statistical analysis, using a level of significance of 5%. Normality tests will be performed in order to check all study data. Categorical variables will be interpreted with Pearson Chi-Square test and being presented as numerical or percentage values respectively. Continuous variables will be presented in the form of a mean value +/- SD and will be compared using the Student test for variables with gaussian distribution and Mann–Whitney test for variable with non-gaussian distribution.

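### Section 2.11 gives repeated LV and NT-proBNP measures a single unadjusted rule, so a follow-up comparison of the hs-CRP groups mixes starting differences with later remodeling and loses precision

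*Protocol article*

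**What the plan says.** - **Tests.** Section 2.11 (Statistical analysis) names the Pearson chi-square test for categorical variables. Continuous variables "will be compared using the Student test for variables with gaussian distribution and Mann–Whitney test for variable with non-gaussian distribution". It does not say whether the Student test is paired or unpaired, whether levels or changes are compared, or what use is made of earlier values.
- **Groups.** Section 2.5: "Study subjects will be distributed in 2 groups", defined by hs-CRP at day 7. Section 2.1 calls the cohort non-randomized.
- **Objective.** Section 1.2 puts ventricular remodeling in the primary objective. Secondary objective 1 is "to assess the effect of systemic inflammation on the structural remodeling process of the left ventricle (LV) following an AMI".
- **Repeated echo.** Section 2.6.2: "Transthoracic echocardiographic (TTE) assessment will be performed at first and last follow-up visit in all patients". The visit lists in section 2.9 instead place echo at day 0 and at months 3, 6, 9 and 12. Echo supplies LVESV, LVEDV and LVEF.
- **Repeated NT-proBNP.** Section 2.6.1: "levels will be evaluated at randomization and at the last follow-up visit".
- **Inflammatory markers.** The Abstract places them "in the acute phase of the myocardial infarction (MI) and at 1 month", but the month-1 visit list (section 2.9.3) shows no blood sample.

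**The concern.** Remodeling is a change in the ventricle over time. The article treats it that way in its Discussion, where it cites LV end-diastolic dilatation of more than 20% at 6 months and greater increases in LV volumes.

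The hs-CRP groups form themselves. Section 1.1 says that myocardial injury triggers the inflammatory cascade, and the Discussion links the extent of injury directly to progression towards heart failure. Patients with high hs-CRP at day 7 may therefore have had a larger or weaker ventricle at day 0.

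A Student or Mann-Whitney test of month-12 volumes would then count that starting difference as part of the inflammation effect. It would also carry all the between-patient spread in starting LV size. The day-0 echo and early NT-proBNP values that would address both problems are already collected, but the analysis gives them no role. What is at stake is the interpretation and the precision of the remodeling comparison in 100 patients.

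**Working it through.** **The plan's own figure.** Section 2.10 states that "a sample size of 50 subjects per group presents a 90% power to detect an increase in major adverse CV events rates proportion of 3.28". This concerns an event proportion and gives no reference rate, so it cannot be reproduced without an assumption. Read as a risk ratio, it gives 90% power only at a reference rate of about 12% to 12.5%. It says nothing about LV measures, and only the 50 per group is used below.

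**Inputs.** From the plan: 50 per group and two-sided alpha 0.05. Assumed: a true difference of 0.5 SD, correlation rho between earliest and follow-up value of 0.3 to 0.7, and equal SDs at both times.

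**Step 1: is the named test valid between groups?** Yes. For the unpaired t test on change scores between two groups of 50, the simulated rejection rate under no difference is 5.1%, 5.0% and 5.0% at rho 0.3, 0.5 and 0.7.

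**Step 2: what a follow-up-only comparison estimates.** If the groups differ by D at day 0 and inflammation has no later effect, the expected follow-up difference is rho × D. With rho 0.3 to 0.7, 30% to 70% of the day-0 gap appears as if it were an effect on remodeling.

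**Step 3: precision.** Power ≈ Φ(d / (s × √(2/n)) − 1.96), with d = 0.5, n = 50 and √(2/50) = 0.2. Unadjusted, s = 1. Adjusted for the earliest value, s = √(1 − rho²), which assumes that group is unrelated to baseline.

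| Analysis | s | d/(0.2s) | Power (normal) | Power (noncentral t) |
|---|---|---|---|---|
| Follow-up only | 1 | 2.500 | 70.5% | 69.7% |
| Adjusted, rho 0.3 | 0.954 | 2.621 | 74.6% | 73.7% |
| Adjusted, rho 0.5 | 0.866 | 2.887 | 82.3% | 81.5% |
| Adjusted, rho 0.7 | 0.714 | 3.501 | 93.8% | 93.4% |

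Change scores, with s = √(2(1 − rho)), give 56.1%, 70.5% and 89.8% (normal), below the adjusted model at each rho.

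**Step 4: if group and baseline are correlated.** With correlation r between group and earliest value, s² becomes (1 − rho²)/(1 − r²). At rho 0.5:
- r = 0: 0.75, power 82.3%.
- r = 0.3 (assumed): 0.75/0.91 = 0.824, s = 0.908, 2.5/0.908 = 2.754, power Φ(0.794) = 79%.
- r = 0.5: 0.75/0.75 = 1, power 70.5%, so no gain in precision is left.

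In the last two cases the unadjusted test is no longer an equal alternative, because by Step 2 it estimates a different quantity.

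**Step 5: early versus late values in the same patients, if such a test were made.** The actual level of an unpaired test on correlated pairs is 2(1 − Φ(1.96/√(1 − rho))): 1.9% at rho 0.3, 0.6% at 0.5 and 0.03% at 0.7. This is below 5%. For a 0.3 SD change in 100 patients, simulated power of Mann-Whitney is 54% to 57%, against 70%, 84% and 97% for the Wilcoxon signed-rank test.

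**The case against.** The strongest reply is that the named tests suit the only comparison the article sets up, which is between two different sets of patients. That stands. Three stronger readings are tempting, and the document does not support them.

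- **That within-patient change is tested with the wrong error rate.** No section plans an early-versus-late test. The Student test has a paired form, and only Mann-Whitney is unambiguously for independent samples. The reference in section 2.11 to all the analysis describes the software and does not make the test list exhaustive. Persistence of inflammation is defined by a single day-7 value, not by a paired change.
- **That false positives would rise.** With positively correlated pairs the error is conservative: changes would be missed.
- **That inflammatory markers are a settled repeated measure.** The month-1 repeat rests on the Abstract alone.

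It can also be said that a condensed article may leave paired tests and models to a fuller plan, and that a test of change scores would fit section 2.11 as written. Both are fair, and silence on paired tests alone would be missing detail. But the article does state a rule for continuous data. That rule is unadjusted, although the article itself links extent of injury to both inflammation and outcome. A specific better method is available from data already collected.

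Finally, the Abstract and sections 2.6 and 2.6.3 also assess remodeling by CMR, which is scheduled once, at month 1, as is dobutamine echo. Those measures have no earlier value to adjust for. This limits the point to serial echo and NT-proBNP.

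**Conclusion.** The point holds in limited form. The rule in section 2.11 is valid at the 5% level between the hs-CRP groups. Applied to follow-up values alone, it does not separate starting LV status from later remodeling, and it loses precision. Under the stated assumptions the loss is about 4 to 24 percentage points of power (69.7% against 73.7% to 93.4%). It is smaller, and can vanish, as group and baseline become correlated. The correlations and the 0.5 SD difference are assumptions, and an even 50/50 split is not guaranteed when a biomarker forms the groups. The primary outcome's chi-square test and the single month-1 CMR and dobutamine measures are not affected.

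**What to change.** 1. In section 2.11, state that the hs-CRP groups are compared on follow-up LVEDV, LVESV, LVEF and log NT-proBNP with a linear model that includes the patient's earliest value. Where echo is available at several visits, use a mixed model with group, visit, group-by-visit, the earliest value and within-patient correlation, and take the month-12 group contrast as the result.
2. Add that any early-versus-late comparison in the same patients uses the paired t test or, for non-Gaussian differences, the Wilcoxon signed-rank test, not Mann-Whitney.
3. Reconcile the echo schedule (section 2.6.2 against sections 2.9.1, 2.9.4 and 2.9.5) and the month-1 biomarker sample (Abstract against section 2.9.3), because these decide which values count as earliest and which visits enter the model.

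The cost is a change of wording, a little more analysis work and possibly software that fits such models. No new patients, visits or measurements are needed. There are two downsides to state in the plan. The day-0 value may already include early effects of the infarct, so the contrast is for change after day 0. In non-randomized groups, adjustment may also change the estimate as well as its precision.

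### Section 2.11 names the Student t-test with no safeguard for unequal variances, in groups whose sizes an hs-CRP cut decides; Welch's test would hold the 5% level at small cost

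*Protocol article*

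**What the plan says.** Section 2.11 (Statistical analysis) gives one rule for continuous variables. It starts with "Normality tests will be performed in order to check all study data". Gaussian variables "will be compared using the Student test for variables with gaussian distribution", and the others go to the "Mann–Whitney test for variable with non-gaussian distribution". The level is 5%, and Section 2.10 makes it two-sided for the sample size. Neither section mentions the equality of variances or a form of the t-test that does without it.

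The groups come from a marker measured after enrolment. Section 2.10 (Sample size) puts it this way: "On the basis of the persistence of systemic inflammation at 7 days after the acute event patients will be allocated into 2 subgroups". Section 2.5 sets the cut at an hs-CRP of 3 mg/dl. No quota, median split or matching is described. Section 2.10 nevertheless plans on equal groups: "a sample size of 50 subjects per group presents a 90% power".

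**The concern.** The pooled t-test assumes normality and equal variances, and the plan checks only the first. With equal group sizes the second hardly matters. With unequal sizes it does: the pooled variance is weighted towards the larger group, while the true variance of the difference in means is dominated by the smaller one. If the smaller group is the more variable, the standard error is too small and false positives rise. If the larger group is the more variable, the test becomes conservative and power is lost.

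Here the sizes are left to the hs-CRP cut. The objectives in Section 1.2 concern plaque vulnerability, viability and remodeling, much of which is measured on continuous scales such as LV volumes, ejection fraction and scar. For those judged Gaussian, the Student test is the only two-group method the article names.

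**Working it through.** **The plan's own figure.** The 50 per group in Section 2.10 was computed for MACE proportions, not for a continuous variable. It cannot be reproduced, because no baseline MACE rate is given. If 3.28 is read as a rate ratio, the stated 90% needs a lower rate of about 12% (12% against 12 × 3.28 = 39.4% gives power 89.1%). For the present point it supplies only the planned split, 50/50.

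**Inputs from the article.** Total N = 100; two-sided 5%; Student test for Gaussian variables; groups formed by the day-7 hs-CRP cut.

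**Inputs assumed, because the article does not give them.** Split from 50/50 to 10/90; ratio of the two SDs 1.5 or 2, in either direction; Gaussian data.

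**Formula.** With group sizes n₁, n₂ and SDs s₁, s₂, the pooled test uses on average

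V_pooled = [((n₁−1)s₁² + (n₂−1)s₂²)/(n₁+n₂−2)] × (1/n₁ + 1/n₂),

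while the true variance is V_true = s₁²/n₁ + s₂²/n₂. The approximate actual level is 2 × [1 − Φ(1.96 × √(V_pooled/V_true))].

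*30/70, smaller group with twice the SD.* V_pooled = [(29×4 + 69×1)/98] × (1/30 + 1/70) = 1.888 × 0.04762 = 0.0899. V_true = 4/30 + 1/70 = 0.1476. The ratio is 0.609 and its root 0.780; 1.96 × 0.780 = 1.53, so the level is about 12.6%.

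*30/70, larger group with twice the SD.* V_pooled = [(29×1 + 69×4)/98] × 0.04762 = 3.112 × 0.04762 = 0.1482. V_true = 1/30 + 4/70 = 0.0905. The ratio is 1.638 and its root 1.280; 1.96 × 1.280 = 2.51, so the level is about 1.2%.

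*50/50, SD ratio 2.* V_pooled = [(49×4 + 49)/98] × 0.04 = 0.10, and V_true = 4/50 + 1/50 = 0.10. The ratio is 1, so the level is 5%.

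**Simulation** (100,000 data sets per cell, equal means). Each entry is the level of the Student test, first with the larger SD in the larger group, then with it in the smaller group.

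| Split | SD ratio 1.5 | SD ratio 2 |
|---|---|---|
| 50/50 | about 5% either way | 5.2% / 5.2% |
| 40/60 | 3.5% / 7.0% | 2.8% / 8.4% |
| 30/70 | 2.3% / 9.4% | 1.4% / 12.8% |
| 20/80 | 1.4% / 12.1% | 0.5% / 18.2% |
| 10/90 | 0.7% / 15.4% | 0.1% / 24.9% |

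With equal SDs the Student level is about 5% at every split. Welch's test lies between 4.9% and 5.3% in every cell.

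**Does the normality check protect?** It looks at shape, not spread. A two-stage rule (Shapiro-Wilk in each group, then Student or Mann–Whitney) was simulated on Gaussian data with the larger SD in the smaller group. It gave 9.5% at 30/70 with ratio 1.5, 12.9% at 30/70 with ratio 2, and 17.1% at 20/80 with ratio 2. The article names no normality test, so Shapiro-Wilk is an assumption.

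**Cost of Welch when the SDs are in fact equal** (power, Student against Welch): 79.1% against 78.6% at 30/70; 79.6% against 78.5% at 25/75; 79.1% against 77.2% at 20/80; 79.2% against 72.4% at 10/90. At 50/50 there is no material difference.

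**The case against.** Several objections are fair.

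- **The article does not say equal-variance.** Pooling is the ordinary meaning of the Student test, but it remains a reading, and a fuller plan that is not shown could specify the variant. This lowers the weight of the point. It does not remove it, because the article states a named test; if Welch's was intended, the sentence names the wrong one.
- **At the planned 50/50 nothing goes wrong.** This stands. Unequal spread alone does no harm; unequal sizes are needed as well.
- **Neither the split nor any SD is documented.** This also stands, and every size above is conditional for that reason. A reader might infer that the true error rate is 18%, or that it runs from 1% to 18%. The documents do not support that: 18% needs a 20/80 split together with a doubled SD in the smaller group, and the range is not a bound in either direction.
- **The direction is unknown.** A reader might infer that the high-inflammation group is more variable, so that false positives multiply. The article gives no SD by group. The CRP study cited in Section 3 reports a greater increase in LV volumes, which concerns level rather than spread. Inflation also requires the more variable group to be the smaller one, and nothing says which group that will be. The test could equally be conservative.
- **The reach is limited.** The primary outcome (Section 2.8) is an incidence, MACE is a rate, and Section 2.11 sends categorical variables to chi-square. Continuous variables judged non-Gaussian go to Mann–Whitney. None of these uses the t-test.

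**Conclusion.** The point holds as a minor one. Section 2.11 fixes a test that can miss its 5% level when group sizes and spreads both differ, and the design leaves the sizes to an hs-CRP cut. The article lets nobody say how far the level will move, or in which direction. Under an assumed SD ratio of 1.5 the shift is moderate even at 30/70 (about 2% to 9%); the larger figures need a twofold ratio and a marked imbalance. The conclusion rests on reading the Student test as the pooled test and on the assumed splits and SD ratios. It is confined to continuous comparisons treated as Gaussian. It casts no doubt on the analysis of the primary outcome or of MACE.

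**What to change.** In Section 2.11, replace the Student test by Welch's unequal-variance t-test for two-group comparisons of continuous variables treated as Gaussian. For example: *Continuous variables treated as Gaussian are compared between the hs-CRP groups by Welch's t-test, two-sided, at 5%.*

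The change is one sentence and needs no new data. It is not quite free: if the SDs turn out equal, power falls by about 1 point at 25/75, about 2 at 20/80 and up to about 7 at 10/90. Since the split cannot be known in advance, that is a reasonable price.

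Fixing the analysis scale of each variable beforehand, instead of letting a normality test on the study data choose the method, is an optional addition. The point does not depend on it.

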## Discussions

3

This manuscript presents the protocol of a clinical study, conducted in a single center, with the purpose to analyze the link between systemic inflammation, pan-coronary plaque vulnerability, myocardial viability and remodeling in patients who had suffered a recent STEMI.

It is well-known that one of the major factors that trigger an AMI is the systemic inflammation, which has a direct influence on coronary plaque vulnerability, usually related to decreased structural stability.^[26]^ According to histological studies, prone-to-rupture plaques present significant differences as compared with stable obstructive coronary plaques.^[27]^ Those high-risk plaque features associated with the presence of acute coronary syndrome (ACS) have been defined by a series of Angio-CT studies and include larger plaque volume, plaque with low attenuation, positive remodeling, large plaque burden, spotty calcium, and napkin-ring sign. Ruptured plaques, the main cause of MIs, proved to have fibrous caps that contain elevated levels of proteases, including metalloproteinases (MMPs). Histologic studies provide strong associative evidence that MMPs promote plaque vulnerability in humans.^[28]^ Similarly, two overexpression studies give a clear evidence of plaque disruption in the presence of high MMP-9 levels, that are thought to influence the rates of atherogenesis and the stability of atherosclerotic plaques.^[29,30]^

Therefore, one of the study objectives will be to investigate the impact of local inflammatory response, assessed by inflammatory biomarkers and adhesion molecules, on pan-coronary plaque vulnerability based on vulnerability features determined via coronary CT angiography, following an AMI.

Patients with AMI who survive the acute event very often present significant deterioration of their clinical status with progression towards heart failure, which is directly linked to the extent of myocardial injury and the remodeling process starting immediately after infarction. At the same time, 20% of patients surviving an AMI present a recurrent cardiovascular event in the following 12 months, as a result of increased systemic inflammation triggered by the infarction, which leads to vulnerabilisation of other atheromatous plaques from all the circulatory system in the post-infarction period. While the role of inflammation in acute coronary events is well established, the impact of inflammatory-mediated vulnerability of coronary plaques from the entire coronary tree on the extension of ventricular remodeling and scaring has not been elucidated so far.

Inflammatory response triggered by MI leads to appropriate infarct healing process and cardiac repair. Despite its beneficial effect, inflammatory reaction present in post AMI phase is a double-edged sword that in association with a vulnerable plaque, vulnerable blood and vulnerable myocardium can lead to catastrophic events, causing postinfarction remodeling and heart failure.^[26,31]^ Based on multivariate analyses, a series of previous studies reported a severe inflammatory response, expressed by serum CRP levels >20 mg/dl, as an independent strong predictor of subacute cardiac rupture and ventricular aneurysm.^[31]^ Furthermore, a prospective study has demonstrated an association between inflammation and LV remodeling, as the group of patients with peak CRP level above the median had a greater increase in LV volumes both at 2 weeks and at 6 months.^[31]^

In recent studies, CMR parameters, including infarct size assessed by LGE, have been extensively evaluated in predicting late LV function in patients with AMI undergoing primary percutaneous intervention (PCI), providing powerful surrogate markers of outcomes.^[32]^ At a clinical level, infarct size proved to be an independent prognostic factor for heart failure, arrhythmic events, and cardiac mortality.^[33]^ In PROTECTION AMI CMR study, the infarct size evaluated by LGE-CMR on day 3 to 5 proved to be the most robust independent predictor of late LVEF and adverse LV remodeling, at 90 days post STEMI.^[34]^ Negative remodeling, based on the cut-off value of >20% left ventricle end-diastolic (LVED) dilatation at 6 months follow-up, proved to have prognostic importance in 2 large multicenter trials.^[35]^ Moreover, in a study conducted by Haeck et al, NT-proBNP proved to be the strongest independent predictor of LV function, assessed by CMR imaging, in patients with STEMI undergoing PCI.^[36]^ As smaller previous studies have reported, admission levels of NT-proBNP above 260 pg/ml proved to be in a strong correlation with LV remodeling and impaired cardiac function during long-term follow-up.^[3]^

